## Abstract

**Background:**

Shared decision making is particularly important in situations with different treatment alternatives. For the treatment of idiopathic Parkinson disease, both pharmacological and surgical approaches can be applied.

**Objective:**

In this research project, a series of studies will be conducted to investigate how decision aids for patients with idiopathic Parkinson disease should be designed in order to support the decision-making process.

**Methods:**

In Study 1a, qualitative interviews will be conducted to determine which needs frequently occur for patients with idiopathic Parkinson disease. In Study 1b, the identified needs will then be rated for personal relevance by an independent group of patients in an online survey. In Study 2, a randomized controlled trial will be used to pretest different decision aids in a sample group of people who do not have a medical background and who do not have Parkinson disease. In Study 3, a randomized controlled trial will be used to investigate the effect of the decision aids that had been evaluated as positive in Study 2 with patients who have idiopathic Parkinson disease.

**Results:**

This series of studies received ethical approval in January 2020. As of June 2020, data collection for Study 1a has started, and it is estimated that Studies 1a, 1b, 2, and 3 will take approximately 4, 4, 6, and 6 months to complete, respectively. It is planned to present the results and analyses at international conferences and to submit the results to peer-reviewed journals for publication, once the studies have been completed. The findings will also be shared with clinicians and patients through presentations at information events.

**Conclusions:**

This series of studies is intended to result in an evidence-based decision aid for patients with idiopathic Parkinson disease in order to support the informed and reflected shared decision-making process. We further intend to contribute to a deeper understanding of the individual preferences of patients with idiopathic Parkinson disease and the impact of those preferences on treatment decisions.

## Introduction

### Background

Shared decision making has become increasingly common in the context of medical consultations [1-3]. While in any medical consultation it is useful and ethically necessary to inform and educate a patient thoroughly, participatory decisions are particularly appropriate in situations where different alternatives need to be considered and for which no one treatment is superior to the others. In these situations, a preference-sensitive decision should be made based on the personal circumstances and individual preferences of the patient [4-6]. Research indicates that patient participation in the medical decision-making process has positive effects. A meta-analysis [7] with a total of 105 studies showed that shared decision making led to increased knowledge, higher confidence in decisions, and more active patient participation. Studies [7,8] found that the use of shared decision making could reduce health care system costs, because patients often chose less invasive (and therefore, less expensive) treatment options. In addition, most patients would like to be more involved in the medical decision-making process [9]. But, despite these promising findings, shared decision making has not yet been sufficiently implemented in clinical practice [10,11]. The Revised Program Theory for shared decision making [12] identified relevant factors influencing engagement in shared decision making. The authors of that paper [12] explicitly foster future research using this theory and examining additional key mechanisms of shared decision making. Based on these theoretical considerations, herein we will examine the influence of health care system support through decision aids.

### Treatment of Parkinson Disease

For the treatment of idiopathic Parkinson disease, both pharmacological and surgical methods can be used. The 2016 *Leitlinien für Diagnostik und Therapie in der Neurologie–Idiopathisches Parkinsonsyndrom*
*(Guidelines for Diagnosis and Therapy in Neurology–Idiopathic Parkinson Disease)* of the *Arbeitsgemeinschaft der Wissenschaftlichen Medizinischen Fachgesellschaften (Association of the Scientific Medical Societies)* and the *Deutsche Gesellschaft für Neurologie (German Society of Neurology)* [13] recommended offering subthalamic nucleus–deep brain stimulation to patients with a confirmed diagnosis of idiopathic Parkinson disease who, despite best medical treatments, have motor fluctuations and dyskinesia that cannot be treated with medication, or tremor that cannot be controlled with medication (recommendation 47 in [13]). In addition, deep brain stimulation of the subthalamic nucleus can be offered to patients 60 years of age or younger with confirmed idiopathic Parkinson disease in the first three years after the onset of motor fluctuations or dyskinesia (recommendation 48 in [13]).

Furthermore, it was emphasized that when data suggest deep brain stimulation rather than best medical treatment, surgical treatment should remain an individual decision as long as medical alternatives exist [13]—even if the outcome of drug treatment may be worse than that of subthalamic nucleus–deep brain stimulation in such cases. Nevertheless, since subthalamic nucleus-deep brain stimulation may be more effective than pharmacological treatment, this surgical alternative should be discussed with the patient. When deciding between subthalamic nucleus–deep brain stimulation or drug therapy, patients should be involved in the decision-making process in order to be able to make a preference-sensitive decision with the physician (recommendation 66 in [13]).

### Shared Decision Making

Doctors in clinical practice often have too little time for lengthy conversations and tend to overestimate the understanding and health literacy of patients [14,15]. Low health literacy of patients with idiopathic Parkinson disease has been shown to correlate with an increased risk of hospitalization [16]. A meta-analysis showed that the perception of traditional role models, in which doctors are the experts whose instructions are followed, represents a barrier for many patients to actively participating in the decision-making process [17]. One way to deal with this barrier is to use decision aids. They are often used to provide information about illnesses and treatment options and have shown their value in various medical fields [18,19]. Decision guidance is an opportunity to support both patient education and informed decision-making in cooperation with attending physicians and therapists. It is explicitly emphasized that decision aids should not claim to replace patient to doctor direct contact or conversations. Rather, they should be viewed as a supplement that makes it easier to take individual needs into account. The guidelines [13] also recommended that patients with idiopathic Parkinson disease should be provided with individually adapted need-based enhanced communication throughout the course of their disease (recommendation 67 in [13]). According to the Revised Program Theory [12] of shared decision making, giving patients support for shared decision making (for example, by means of a well-designed decision aid) may result in higher confidence in their decision-making abilities and in stronger engagement in shared decision making. Studies [20-22] showed that many patients with Parkinson disease want to play a more active role in treatment decisions [20]. As one study [21] that interviewed patients with Parkinson disease showed, patients often had to take the initiative themselves to be referred to a deep brain stimulation center. Only 10% to 15% of patients for whom deep brain stimulation might be considered a suitable therapy option were, in fact, referred to specialist centers. This finding can be attributed, among other reasons, to insufficient information on the part of patients and neurologists alike [22].

### Decision Aids

There are many ways to support patients in their decision-making process and to inform them about the disease and its possible treatment alternatives. Experience reports (ie, narratives) from other patients are an important source of information in addition to exchanges with medical specialists. Patients exchange information about their situation with other people and use the internet in their search for medical information often finding testimonials from other patients [23]. Patient reports are also often integrated into decision-making aids. The use of narratives in decision aids is critically discussed in the literature [24-26]. Narratives have the advantage that they are vivid, easy to understand, and not too abstract, which can make it easier for patients to process and remember the information conveyed [24,27]; therefore, this format appears to be particularly suitable for patients with idiopathic Parkinson disease, as their cognitive abilities may also be limited. Entwistle et al [28] concluded, in a qualitative interview study, that the personal experiences of others combined with the imparting of factual knowledge can be very helpful for decision making. The patients who were interviewed stated that the reports helped them to better imagine the different options, to become clear about what was important to them personally, and to handle their negative emotions; however, narratives can also have the disadvantage of encouraging the activation of heuristics and generating additional emotions, which can lead to a distorted perception of the information given [25]. In a study [29] with a focus on persuasion, it was found that information mediation with narratives, when compared with scientific information mediation, led to more knowledge gained, more emotions, and stronger persuasion. Narratives also partly influenced the decisions of people who do not have a medical background [30]. In preference-sensitive decision situations, where the needs of the patient should be a key factor in the decision, the persuasive effect of decision support would be considered problematic. The decision-making process of patients should be supported in the preference-sensitive situations that occur in patients with idiopathic Parkinson disease, without convincing them of any one of the possible treatment options. According to the Expected Utility Theory [31,32], it is easier for patients to engage in shared decision making if outcome probabilities of a given treatment are presented. But in preference-sensitive situations, no treatment is superior to the other. As a result, decision difficulty in these situations would be perceived as rather high [12]. The question arises as to whether it makes sense in this situation to report clinical outcomes at all, or whether it is more useful to provide information about possible personal motives and preferences. Decision aids and narratives can be designed very differently and can exert various positive or negative influences on decision making as a result of their design. It is important to understand how decision aids should be designed to help patients take their knowledge, their personal preferences, and their needs into account when making decisions, without pushing them in any specific direction.

### Goals of the Research Project

In this research project, a series of studies will be conducted to investigate how decision aids for patients with idiopathic Parkinson disease should be designed in order to support the decision-making process. The goal is to support patients in taking their individual preferences into account when making a decision and to make them feel confident with their decision. We will use a participatory design process for the development of the decision aid [33]. Feedback and ideas for improvement will be requested from health care professionals before the prototype is used in the studies.

It is an open question whether the presentation of possible preferences has a positive influence on the decision-making process. In addition, it has not yet been clarified whether patient narratives can strengthen patient decisions in difficult decision situations. Moreover, we will act on the suggestion of the Revised Program Theory and examine additional key mechanisms of shared decision making. We aim to compare the impact of presenting motives that affect a decision with the impact of presenting treatment outcomes.

In Study 1a, qualitative interviews will be conducted to determine which needs frequently occur for patients with idiopathic Parkinson disease. In Study 1b, the identified needs will then be assessed for personal relevance by other patients in an online survey. In Study 2, a randomized controlled trial will be used to pretest different decision aids with people who do not have a medical background and who do not have Parkinson disease. In Study 3, a randomized controlled trial will be used to investigate the effect of the decision aids that were evaluated as positive in Study 2 in patients with idiopathic Parkinson disease.

## Methods

### Ethical Approval

These proposed studies have been reviewed and approved by the ethics committee of the Faculty of Medicine of the Eberhard Karls University Tübingen.

### Studies 1a and 1b: Expectations and Wishes Regarding Medical Treatment Options for Parkinson

#### Study Design

A qualitative interview study (Study 1a) with 6 patients with idiopathic Parkinson disease will identify the common needs, expectations, wishes, and preferences that play a role in the decision to opt for drug-only treatment over deep brain stimulation. Patients with idiopathic Parkinson disease who qualify for deep brain stimulation treatment according to recommendations 47 and 48 in [13] will be invited to a screening week as part of regular clinical care.

During this 1-week inpatient stay, the medical, cognitive, and psychological condition of patients will be examined in preparation for potential deep brain stimulation surgery. From a certain date onward, all patients who meet the inclusion criteria (see below) will be asked by the treating physician whether they agree to participate in a qualitative interview. A semistandardized interview lasting approximately 30 minutes will be conducted with those who agree to participate in order to identify the personal needs, hopes, fears, and expectations associated with drug treatment and deep brain stimulation treatment options. In an online survey study (Study 1b), a different group of patients with idiopathic Parkinson disease will rate the needs, hopes, fears, and expectations that were identified in Study 1a according to personal relevance. Patients with idiopathic Parkinson disease who are at different stages of their disease will be recruited for Study 1b. Patient assessment of their stage and burden of the disease will be measured using a validated questionnaire (Parkinson Disease Questionnaire, PDQ-39) [34].

#### Participants

In order to achieve a representative rating, a total of 60 patients will be recruited for the online survey study (Study 1b). Recruitment will be carried out with the support of the specialized outpatient units of the University Hospital Tübingen, neurologists in private practice, and self-help groups for patients with idiopathic Parkinson disease. Patients will be included if they have been diagnosed with Parkinson disease, have had Parkinson disease for at least 5 years, are between 18 and 80 years of age; have taken prescribed dopaminergic medication consistently for at least two weeks before inclusion in the study; have a very good knowledge of German, and have signed a written declaration of consent. Patients will be excluded if they have been diagnosed with dementia.

#### Study 1a: Interview Guide

During the interview, each area will be introduced with an open question (Textbox 1). Further questions will follow only if the answer is unclear or the question has not been answered.

Open-ended questions and topics for semistructured interview.
**Satisfaction with the current situation**
How satisfied are you with the current situation? (scaling question: 0 = very dissatisfied, 100 = very satisfied)What should remain the same?What should change?Other: mobility and motor skills, faculty of speech, sleep, memory and concentration ability, previous treatment, general state of health, execution of profession and hobbies, participation in social life
**Reasons and expectations**
What are your main reasons for deep brain stimulation?What are your main reasons for a purely pharmacological therapy?What are other reasons?What should change?How would you know if the decision was good?In which area (eg, work, social life, hobbies) do you hope to have a positive influence?What are your plans for the time after the deep brain stimulation/drug changeover?What positive expectations/worries do you associate with a deep brain stimulation/drug changeover regarding your social environment, your self-reliance, your well-being?

#### Study 1b: Questionnaire

The needs, wishes, and worries that are identified in Study 1a will be evaluated in Study 1b. Patients who wish to participate will also have to confirm that they are currently in the process of deciding between further treatment with medication or deep brain stimulation. The questionnaire will initially present questions pertaining to inclusion and exclusion criteria, and if their responses indicate they are eligible, questions about personal needs, wishes, and worries will be provided.

A maximum of 20 statements such as (the following are example items only) “I hope to be able to maintain more personal contacts through a successful treatment”, “It is important to me that the treatment has as few side effects as possible,” and “I hope that the treatment will improve my independence” will be evaluated. In addition, participant knowledge about treatment options will be evaluated with maximum of 20 statements or questions such as (the following are example items only) “The danger that deep brain stimulation can lead to psychological impairment is very high” and “The danger that a purely pharmacological treatment can lead to psychological impairment is very high” where participants will indicate whether the statements are true or false and how confident they are in their answers:. Since patients with idiopathic Parkinson disease may display neuropsychiatric symptoms, such as apathy or emotional instability, the German version of the Apathy Evaluation Scale [35] and a German version of a short-scale for assessing the personality traits in the five-factor model (big five) [36] will be administered.

### Study 2: Effects of Decision Aids on the Decision-Making Process (People With Nonmedical Background)

#### Study Design

Based on the patient preferences identified in Study 1, online decision aids will be designed in close collaboration with health professionals. We will use a participatory design process to increase the later acceptance and use of the decision aids, and thus, facilitate the implementation process in clinical practice. The impact of the decision aids on the decision-making process will be investigated in a randomized controlled trial with a 1×3 between-subject design with the following 3 groups: condition 1, decision aid with factual information (control); condition 2, decision aid with factual information and patient reports on the individual motives underlying the decision-making process; and condition 3, decision aid with factual information and patient reports on the outcomes achieved through the treatment option.

In condition 3, positive and negative outcomes will be presented according to the actual success rate of the treatment options, that is, both successful and less successful treatment outcomes will be shown for both treatment options. The information provided to the participants regarding the success rates of the treatment options will be based upon existing literature in line with institutional history.

We hypothesize that the conditions containing patient reports on motives or outcomes will have a beneficial effect compared to the condition with only factual information; participants to whom decision aids with patient reports are presented will feel better prepared for decision making (Hypothesis 1) and will evaluate the decision more positively (Hypothesis 2). It is an open research question whether the two conditions with patient reports on individual motives and patient reports on outcomes will also differ with respect to preparation for decision making and decision evaluation.

In addition, this study will be used to evaluate and refine the factual information part of the decision aid. Participant knowledge about treatment options will be evaluated pre and posttest to identify which facts are difficult to understand (and which, perhaps, even result in misunderstandings or irrational fears). This information will influence the design of the factual information and will be re-evaluated in the subsequent study (Study 3).

#### Participants

Healthy individuals who are neither active in the medical field nor studying a medical subject will be recruited via the Leibniz Institut für Wissensmedien database of test subjects and the University of Tübingen email distribution list, where individuals who are not studying medical-related subjects can be preidentified. Participants at least 18 years old, not affected by Parkinson disease, and with a very good knowledge of German will be eligible for inclusion.

Since only medium to large effect sizes are relevant for our purposes, a sample size of 37 participants per condition will be targeted. The sample size was determined using G*Power [37] and is based on an alpha error probability of .05, a test power of .90, and an expected effect size of *f*=0.30 for an analysis of variance with repeated measurements and between-subject factors.

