#### Procedure

After basic demographic data (age, gender, education) and individual prior experiences with Parkinson disease have been collected, the study participants will be asked to put themselves in the position of a patient with idiopathic Parkinson disease with the help of a case description. The following dependent variables will be measured as target variables before and after the use of the decision support: decisional conflict [38]; hypothetical decision (which treatment option would be preferred); attitude toward both treatment options (modified according to [39]); and knowledge about risks and side effects of treatment options, mode of action of treatment options, and possible advantages and disadvantages of treatment options.

Subsequently, participants will be randomly assigned (computer-generated assignments) to the 3 conditions. Based on the results of Study 1a and Study 1b, a text- and video-based decision aid will be designed with a maximum reception time of 15 minutes.

In addition, the following are to be completed after the decision aid has been used: preparation for decision making (based on [40]); evaluation of the preferences or motives identified in Study 1 with regard to the importance for the decision made, decision evaluation scale [41]; reflection on one’s own reasons for the decision; suggestions for improvement (open answer format), and the knowledge test.

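### Study 2: the 90% power for 37 per condition comes from a repeated-measures calculation, but the outcomes of Hypotheses 1 and 2 are measured once, so the omnibus one-way ANOVA has about 80%

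*Protocol article*

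**What the plan says.** All references are to Study 2 in the protocol article.

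- **Participants:** "a sample size of 37 participants per condition will be targeted", based on "an alpha error probability of .05, a test power of .90" and "an expected effect size of *f*=0.30". The test named for the calculation is an "analysis of variance with repeated measurements and between-subject factors".
- **Study Design:** a "1×3 between-subject design with the following 3 groups". The two hypotheses are that participants who see patient reports "will feel better prepared for decision making (Hypothesis 1) and will evaluate the decision more positively (Hypothesis 2"). Whether reports on motives and reports on outcomes differ from each other is left as an open question.
- **Procedure, measured twice:** "The following dependent variables will be measured as target variables before and after the use of the decision support". The list holds decisional conflict, hypothetical decision, attitude and knowledge. Neither hypothesis scale is in it.
- **Procedure, measured once:** "the following are to be completed after the decision aid has been used: preparation for decision making (based on [40"). The decision evaluation scale is in this second list too. The Measures section also labels the preparation scale as postintervention.
- **Analysis:** analysis of variance with post hoc tests for interval-scaled data and Mann-Whitney tests for ordinal data. No planned contrast and no covariance analysis is named.

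**The concern.** A repeated-measures calculation for a between-subject factor treats each participant as supplying the average of several correlated measurements. That lowers the error variance and so the required sample size. The gain is not available for an outcome recorded once, and both hypothesis outcomes are recorded once. The stated sample size, stated power and measurement schedule therefore cannot all hold for the hypotheses that Study 2 sets out to test.

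The article would be promising a 10% risk of missing an effect of f=0.30 when the risk in the omnibus test is about 20%. A non-significant result for either hypothesis would look more conclusive than it is.

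**Working it through.** **Inputs.** From the article: 3 groups, 37 each (N = 3 × 37 = 111), alpha 0.05, f=0.30, stated power 0.90. The number of measurements, m=2, is inferred from the before-and-after schedule. The correlation between measurements is not stated; 0.5 is an assumption. Power is the upper tail of the noncentral F distribution with noncentrality λ.

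**Step 1: reproduce the stated figure.** For the between factor of a repeated-measures ANOVA, λ = f²·N·m / [1 + (m−1)ρ], with 2 and N−3 degrees of freedom.

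- N=108: λ = 0.09 × 108 × 2 / 1.5 = 12.96, power 0.899.
- N=111: λ = 0.09 × 111 × 2 / 1.5 = 13.32, power 0.907.

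The smallest balanced total reaching 90% is 111, that is 37 per condition, as stated. Alternatives do not give 111. At ρ=0.5 the group-by-time interaction needs 39 and the within factor 33. Three or four measurements need 99 or 93. A one-way ANOVA needs 144.

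**Step 2: the test that fits one measurement.** For a one-way ANOVA, λ = f²·N, with 2 and N−3 degrees of freedom.

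- N=111: λ = 0.09 × 111 = 9.99, power 0.803.
- N=141: λ = 12.69, power 0.894. N=144: λ = 12.96, power 0.901. So 90% needs 144, or 48 per condition.
- At N=111, f=0.34 gives power 0.896, so the f detectable with 90% power is about 0.34.
- At N=111, power is 0.638 for f=0.25 and 0.913 for f=0.35.

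None of the Step 2 results depends on the assumed correlation or on m.

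**Step 3: the directional comparison, both report conditions against facts only.** The two-sided contrast has standard error √(1/37 + 1/74) = 0.2013 in SD units and 108 degrees of freedom. Its power at f=0.30 depends on how the means are arranged:

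| Means (facts, report A, report B) | Contrast | Noncentrality | Power |
|---|---|---|---|
| Reports equal: 0, 0.636, 0.636 | 0.636 | 3.16 | 0.88 |
| Evenly spaced: 0, 0.367, 0.735 | 0.551 | 2.74 | 0.77 |
| Only one works: 0, 0, 0.636 | 0.318 | 1.58 | 0.35 |

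**Step 4: the pre/post outcomes.** The first measurement precedes randomisation, so expected baseline means are equal. A between-factor test averages the two time points and halves any post-aid difference: f=0.30 becomes 0.15. The Step 1 calculation, which puts the full f=0.30 on the average, does not describe these outcomes. Tests that use the baseline properly, with f=0.30 on the post-aid score and N=111, give:

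| Correlation | Change score or group by time, λ = 9.99 / [2(1−ρ)] | ANCOVA, λ = 9.99 / (1−ρ²) |
|---|---|---|
| 0.3 | 0.65 | 0.84 |
| 0.5 | 0.80 | 0.91 |
| 0.7 | 0.96 | 0.98 |

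**The case against.** **80% is not the power of every reasonable test of the hypotheses.** This stands. The figure belongs to the two-degree-of-freedom omnibus test. Hypotheses 1 and 2 set report conditions against facts only, and a contrast for that could reach 0.88, near the stated 0.90. But 0.88 requires the two report conditions to be equal, the other arrangements shown give less, and the Analysis section plans an ANOVA with post hoc tests rather than this contrast.

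**The article does not name the scale for Hypothesis 2.** This stands in part. The decision evaluation scale is the natural reading, but the Measures section also lists ratings of feelings about the decision. Hypothesis 1 is unambiguous, since its scale is explicitly postintervention.

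**The pre/post outcomes may be badly underpowered.** A reader might infer this, because the group effect averaged over both times has power of only 0.34 at a correlation of 0.5 (0.31 to 0.39 for correlations 0.7 to 0.3). The article does not support that inference. It does not commit to the averaged effect as the test of the aid, and the group-by-time test has 0.80 at the same correlation.

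**A null result would decide what enters Study 3.** A reader might infer this too. The Study 3 design section says that the most suitable format will be selected, but attaches no significance rule, and Study 2 is described as a pretest.

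**The detail may sit in a fuller document.** This does not help. The point concerns a test, a power and a schedule that the article itself states and that do not agree.

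**Conclusion.** The stated 90% is wrong for Hypothesis 1, and for Hypothesis 2 if its outcome is the decision evaluation scale. The omnibus ANOVA that the article plans has power 0.80 at f=0.30, alpha .05 and 37 per condition, a shortfall of 10 percentage points that doubles the type II error. This conclusion uses only stated inputs. The assumed correlation of 0.5 serves only to show where 37 came from.

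The sample size is not thereby inadequate. It is exactly the smallest balanced size that reaches 80% in the one-way test. What needs correcting is the claim attached to it. For the pre/post outcomes the finding is limited to this: the cited calculation does not describe them.

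**What to change.** 1. Keep 37 per condition. In the Study 2 Participants section, replace the repeated-measures basis with a one-way ANOVA omnibus test and state about 80% power at f=0.30 for Hypotheses 1 and 2. If 90% is wanted instead, the requirement is 48 per condition, 33 more participants in total (144 − 111).
2. Name the outcome scale for Hypothesis 2.
3. If the sponsor chooses to prespecify a contrast of both report conditions against facts only, add it to the Analysis section and quote its power with the assumption attached, as in the Step 3 table.
4. Quote power for the pre/post outcomes only for the test that will be used, over correlations of 0.3 to 0.7: 0.65 to 0.96 for a change score or group-by-time test, 0.84 to 0.98 for ANCOVA.

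Items 1 (at 37 per condition) and 2 are wording only, need no extra participants, and make the stated power less favourable. Adopting the contrast or ANCOVA would change the planned analysis and should be recorded as such.
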